## Summary

Approximately 4–7% of children have asthma requiring regular medication. In addition, an equally large proportion of children experience wheezing episodes triggered by infections. Among all pediatric emergency department visits, about 10% are due to respiratory distress, and up to 40% of these cases lead to hospitalization. Recurrent episodes of respiratory distress affect about 10% of children.

Acute respiratory distress is primarily treated with inhaled salbutamol, a bronchodilator, which is usually administered via a valved holding chamber (VHC). However, there are currently no recommendations on the optimal size or model of spacer device to be used in the treatment of acute respiratory distress. In a recent *in vitro* study conducted in Finland, significant differences were reported between commercially available VHCs in terms of their functional performance. Among these, the OptiChamber Diamond device showed moderately reliable performance. In contrast, the Babyhaler, currently the most widely used spacer in Finland, demonstrated notably low delivery efficiency, particularly at inspiratory flows typical of young children. The measured differences between devices were so substantial that they are presumed to influence clinical treatment efficacy, especially in acute cases.

The aim of this study is to determine whether the differences observed in *in vitro* performance between spacer devices are clinically relevant *in vivo* during emergency treatment. Specifically, the study will assess whether there is a difference between the Babyhaler and the OptiChamber Diamond in the treatment of acute respiratory distress in children in terms of:

1. symptom relief
2. likelihood of hospitalization

- ~~3. recurrence of symptoms (Amended in 25.2.2021. Outcome removed because it was not feasible to collect the data reliably in all the centers)~~
4. treatment acceptance
5. adverse effects.

This is a pragmatic randomized, investigator-blinded, multicenter clinical trial conducted in the pediatric emergency departments of Tampere, Oulu, and Kuopio University Hospitals, as well as at the Terveystalo outpatient clinic in Tampere. The study involves standard clinical care, with no blood samples or additional diagnostic procedures. Both VHCs are approved for pediatric use in Finland and internationally. Salbutamol treatment will follow national evidence-based care guidelines (Käypä hoito).

Based on sample size calculations, the study will include 80 children aged 6 months to 4 years who are diagnosed with moderate or severe bronchial obstruction. In the emergency department, the physician-investigator will assess the child's respiratory distress using a standardized clinical scoring tool. Each child will receive salbutamol (0.6 mg or 0.8 mg, based on weight) up to four times at 20-minute intervals via one of the two VHCs. The investigator will assess clinical response at scheduled intervals and determine whether the child should be discharged or admitted for inpatient care. Other aspects of follow-up and treatment will proceed according to standard clinical protocols.

Randomization lists for each site will be created using block randomization with randomly permuted block sizes of 2, 4, and 6. Each child will have an equal chance of being allocated to either VHC group.

Spacer devices are currently used with the assumption that they are interchangeable. However, recent *in vitro* studies suggest that the devices used in Finland may have substantial differences in drug delivery efficiency. One of the main goals of the Finnish National Allergy Program 2008–2018 was to focus efforts on preventing severe symptoms and asthma exacerbations. Respiratory symptoms related to airway obstruction remain a common issue in children, and reducing their frequency and effectively managing acute episodes is key to minimizing both patient suffering and healthcare costs. It is especially important to evaluate, standardize, and optimize critical treatment practices.

The regional ethics committee of the Tampere University Hospital special responsibility area has approved the study on the 18th of March 2019 (Ethics Committee Code: R19030). Recruitment is expected to begin in spring 2019. The results will be published in both Finnish and international peer-reviewed journals.

## Introduction

### Prevalence of Asthma and Asthma-like Symptoms in Children

Asthma is the most common chronic disease in children that qualifies for special reimbursement by the Finnish Social Insurance Institution (Kela). Approximately 4–7% of children have asthma requiring regular pharmacological treatment. In addition, an equally large proportion of children experience wheezing triggered by infections [1]. Among infants and preschool-aged children, 20–30% experience wheezing at least once during the first few years of life [2].

Children with infection-triggered wheezing, i.e., obstructive bronchitis, place a significant burden on hospitals, and those managed at home lead to significant loss of workdays for parents. Approximately 10% of all visits to pediatric emergency departments are due to respiratory distress, and up to 40% of these cases result in hospitalization [1]. Up to 80% of all return visits to pediatric emergency departments are due to respiratory distress ([name], unpublished data). Recurrent episodes of respiratory distress affect about 10% of children.

## Emergency Treatment of Infection-Triggered Wheezing (Obstruction) with Inhaled Medications

Acute respiratory distress is primarily treated with inhaled salbutamol, a bronchodilator that relieves bronchial smooth muscle constriction. It is administered either via a valved holding chamber (Figure 1) or by nebulizer. Clinical studies have shown no significant difference in treatment efficacy between spacer and nebulizers in the treatment of acute asthma attacks in either adults or children [3-7].

In Finland, spacers are now used as the first-line delivery method in the acute treatment of bronchial obstruction. The medication used is salbutamol in metered-dose inhaler form (0.1 mg per actuation). According to the national evidence-based guideline (Käypä hoito), salbutamol is administered initially at a dose of 4–8 actuations (0.4–0.8 mg) every 20 minutes for 3–4 doses to reverse marked bronchoconstriction, followed by 2–4 actuations every four hours [8].

**Figure 1.** A) In children under the age of 3, inhaled medications are administered via pressurized metered-dose inhaler (pMDI) using a valved holding chamber with a face mask. Shown: OptiChamber Diamond (image © Philips). B) Around the age of 3, most children learn to seal the mouthpiece of the holding chamber tightly with their lips, allowing the mask to be discontinued. Shown: Babyhaler (image © [name]).

[figure not shown]

## Use of Spacer Devices in Finland

Several different models of spacer devices and masks are available on the Finnish market (Table 1). There are no clear recommendations regarding which spacer should be used in the treatment of acute respiratory distress. According to a recent survey ([name] & [name], unpublished data), the Babyhaler brand spacer (Figure 1B and Figure 2) is predominantly used in hospitals and health centers across Finland.

**Table 1.** Spacer devices intended for pediatric use currently available on the Finnish market. Price estimates are based on information provided by online retailers.

| Spacer              | Chamber volume | Face mask volume | Price | Huomioitavaa                                                    |
|---------------------|----------------|------------------|-------|-----------------------------------------------------------------|
| A2A Spacer          | 210 ml         | 80 ml            | 26 €  | One size face mask                                              |
| Aerochamber Plus    | 149 ml         | 35 ml            | 50 €  | Four models, one without a mask, and three different mask sizes |
| Babyhaler           | 350 ml         | 80 ml            | 35 €  | One size face mask                                              |
| OptiChamber Diamond | 140 ml         | 45 ml            | 25 €  | Three face mask sizes                                           |
| Vortex              | 194 ml         | 46 ml            | 45 €  | Two face mask sizes                                             |

**Figure 2.** Spacer devices used in hospital and health center emergency departments. A nationwide survey ([name] & [name]) is currently ongoing, with responses received from 51 out of 100 units across Finland to date. In some units, multiple devices may be used interchangeably. The Volumatic device is not intended for use in children.

[figure not shown]

## Spacer Device Characteristics and Differences

The most important properties of a spacer device that significantly influence the effectiveness of inhaled medication delivery are:

1. the volume of the chamber
2. electrostatic charge
3. the shape and particle size of the aerosol plume
4. valve characteristics
5. mask properties.

In a recent experimental study, the delivery efficiency (fine particle dose) of spacer devices currently available on the Finnish market (Table 1) was measured under standardized in vitro conditions using various breathing rates and inspiratory volumes. Drug delivery efficiency was found to be strongly influenced by the child's breathing pattern and the use of a face mask ([name] & [name], *ERJ Open Res*, in press). In addition, the results demonstrated significant manufacturer-specific differences in the physical characteristics of the devices and, in particular, in the delivery efficiency of salbutamol. For some spacer models, the median delivered dose of salbutamol was as low as less than 1% of the nominal dose (Figure 3). Of the tested devices, OptiChamber Diamond and AeroChamber Plus showed moderately reliable performance both with and without a mask. The Babyhaler, by far the most widely used spacer in Finland, had low delivery efficiency (2.6% without a mask and 0.8% with a mask, relative to the nominal dose).

As early as 1999, Turpeinen et al. [9] reported that the amount of drug reaching the airways through devices from different manufacturers can vary by several-fold. Our own findings confirm earlier observations that spacer devices used for drug delivery should not be considered interchangeable, even if they appear similar externally. Differences between spacers and masks may significantly impact clinical outcomes and could potentially influence the frequency of emergency department visits and hospital

admissions. Each device's performance and usability in pediatric drug delivery must be evaluated individually [10].

## Clinical Problem and Research Question

In studies comparing the effectiveness of spacers and nebulizers in the treatment of acute respiratory distress, a wide variety of spacer devices, both commercially manufactured and custom-made, have been used. Some studies fail to report the type of spacer used at all [3][7]. The efficacy of different spacer devices has not been systematically compared, and no comprehensive, independent (non-industry-funded) studies on this topic have been published. In Finland, national care guidelines (e.g., those available through the Terveystieto medical database) refer to spacers in general terms without addressing specific device characteristics or potential differences that could affect treatment outcomes.

To justify changes to clinical guidelines, *in vitro* findings must be supported by *in vivo* evidence demonstrating significant differences in treatment efficacy. For this study, we selected for comparison the Babyhaler (Figure 1B), currently the most commonly used spacer in Finnish emergency departments, and the OptiChamber Diamond (Figure 1A), which performed well in *in vitro* measurements and is also the most cost-effective option.

## Study Objectives

The objective of this study is to determine whether the device differences observed in *in vitro* measurements have a clinically meaningful impact on treatment success in the emergency setting (*in vivo*). The differences in delivered drug dose between the Babyhaler (BH) and OptiChamber Diamond (OD) devices are substantial (Figure 3). These differences are assumed to affect the bronchodilator treatment response, particularly in young children with moderate to severe respiratory distress. In this patient group, breathing is often highly variable, shallow, and rapid—factors that make the administration of inhaled medications especially challenging.

The study will assess whether there is a difference between the Babyhaler and OptiChamber Diamond in the treatment of acute respiratory distress in children in terms of:

1. Symptom relief (Tables 2 and 3)
2. Probability of hospitalization
3. Symptom recurrence (return visits within 48 hours of discharge)
4. Treatment acceptance (which device children tolerate better; Table 4)
5. Adverse effects

**Table 2.** Respiratory Distress Assessment Instrument (RDAI) scoring [11]

|                    | Points |      |          |        |     | Max. score |
|--------------------|--------|------|----------|--------|-----|------------|
|                    | 0      | 1    | 2        | 3      | 4   |            |
| Wheezing    |        |      |          |        |     |            |
| Expiration         | none   | End  | ½        | ¾      | all | 4          |
| Inspiration        | none   | Part | All      | –      | –   | 2          |
| Lung fields        | none   | Part | All      | –      | –   | 2          |
| Retractions |        |      |          |        |     |            |
| Supraclavicular    | none   | Mild | Moderate | Marked | –   | 3          |
| Intercostal        | none   | Mild | Moderate | Marked | –   | 3          |
| Subcostal          | none   | Mild | Moderate | Marked | –   | 3          |

The maximum score for wheezing is 8, and for the use of accessory muscles 9.  
Diminished breath sounds correspond to 8 points for wheezing.

**Table 3.** Clinical variables monitored and differences between groups

| Main outcomes                             | Secondary outcomes                                                                                                                                                                                                                                                                                                                                                                                                                                                                                                                                                                                                                                                                                                                                                                                                                                                                                                                                                                                                                          |
|-------------------------------------------|---------------------------------------------------------------------------------------------------------------------------------------------------------------------------------------------------------------------------------------------------------------------------------------------------------------------------------------------------------------------------------------------------------------------------------------------------------------------------------------------------------------------------------------------------------------------------------------------------------------------------------------------------------------------------------------------------------------------------------------------------------------------------------------------------------------------------------------------------------------------------------------------------------------------------------------------------------------------------------------------------------------------------------------------|
| RDAI-scores
<del>SaO2</del> | SaO2 (Amended in 13.1.2025. Decision made to have only one primary outcome that was the base of the sample size calculation. SaO2 was moved from Main outcomes to Secondary outcomes)
Change in respiratory rate (difference before and after medication)
Heart rate (difference before and after medication)
<del>Need for oral prednisolone</del> (Amended in 25.2.2021. The proportion of children receiving oral corticosteroids will be reported as baseline characteristic instead of outcome because they were often given before and/or during the intervention)
Number (proportion) of patients admitted to the hospital
Parents' assessment of treatment success (Table 4)
Healthcare personnel's assessment of treatment success (Table 4)
Proportion of patients requiring a fourth dose of medication
<del>Number of return visits</del> (Amended in 25.2.2021. Outcome removed because it is not feasible to collect the data reliably in all the centers) |

**Table 4.** Assessment of treatment adherence and perceived effectiveness of inhalation therapy using a structured scoring system

|                                  | Points |   |   |   |   |   |
|----------------------------------|--------|---|---|---|---|---|
|                                  | 0      | 1 | 2 | 3 | 4 | 5 |
| Evaluated by the nurse           | 0      | 1 | 2 | 3 | 4 | 5 |
| Evaluated by the parent/guardian | 0      | 1 | 2 | 3 | 4 | 5 |

0 = medication administration failed; 1 = child is crying continuously; 2 = child is crying, screaming, or resisting, but not continuously; 3 = child shows some resistance to medication administration but does not cry or scream; 4 = good cooperation, but the child appears uncomfortable; 5 = good cooperation and calm breathing throughout medication administration. Adapted from Minh et al. [11]. If the nurse rates the medication administration as 0–2 points, the same dose is repeated once.

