### Study Population

The study will include a total of 80 children aged 6 months to 4 years who are diagnosed with moderate or severe bronchial obstruction (RDAI score  $\geq 6$ , Table 2), and whose guardians have provided written, informed consent. The severity of respiratory distress is assessed using a previously published Respiratory Distress Assessment Instrument (RDAI) [12, 13].

Children will be excluded from the study at the emergency department if they meet any of the following criteria:

1. Require immediate inpatient care
2. Have an oxygen saturation ( $SpO_2$ ) below 85% upon arrival
3. Are diagnosed with bacterial or viral pneumonia
4. Show inspiratory crackles (suggestive of bronchiolitis in infants)
5. Are diagnosed with acute laryngitis (croup)
6. Are suspected to have or are confirmed to have a foreign body in the airway
7. Have liver or kidney dysfunction
8. Are immunocompromised or have another chronic condition deemed exclusionary by the attending physician
9. Have bronchopulmonary dysplasia due to prematurity
10. Are currently using a long-acting beta-agonist (LABA)
11. Have previously participated in this study
12. Refuse to take medication via spacer
13. Have participated in another clinical trial within the 30 days prior to enrollment

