### **Treatment of the Enrolled Child in the Emergency Department**

The study physician assesses the severity of the child's respiratory distress and records the RDAI score as well as other clinical variables listed in Table 3 on the study form. The child receives salbutamol via either the BH or OD spacer, with a dose based on weight (0.6 mg or 0.8 mg, corresponding to 6 or 8 actuations), up to four times at 20-minute intervals (Figure 4).

The study physician reassesses the clinical variables (Table 3) before treatment and again 20 minutes after the first two doses. If the child still requires bronchodilator treatment, up to two additional doses (0.6 or 0.8 mg, depending on weight) are administered. The physician again assesses breathing effort 20 minutes after the third and, if given, the fourth dose, and then makes the decision regarding further treatment (discharge or hospitalization, Figure 4). Otherwise, the follow-up and care of study participants will proceed in the outpatient clinic according to standard clinical practice.

In children under the age of 3, the spacer is used with a face mask; in older children, it may be used without a mask when appropriate. Salbutamol is administered one puff at a time into the spacer, and after each actuation, the child should take at least five breaths through the device. If the child strongly resists medication administration or is crying (Table 4), the same dose should be reattempted once the child has calmed down.

If a child enrolled in the Chamber study is discharged from the outpatient clinic, they will be given the spacer used during the study free of charge, along with written instructions for continued care. If the child is admitted to the hospital, treatment will continue on the ward using the same spacer device that was used in the emergency department.

**Figure 3.** Median dose of salbutamol delivered from spacer devices (% of nominal dose) and range measured using a filter (in vitro filter dose), when used without a mask (no mask) or with a mask (with mask). Measurements were performed using devices from three different production batches (LOT).

[figure not shown]

RR, respiratory rate. Vt, tidal volume.

LOT, production batch. P-values shown above the bars refer to differences with or without a mask, based on the Mann-Whitney U test.

P-values below the graph refer to differences between devices from different production batches, based on the Kruskal-Wallis test.

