## Statistical analysis

All statistical analyses will be conducted in the intention-to-treat population based on predefined outcome measures, comparing children treated with each of the two valved holding chambers. Continuous variables with normal distribution will be analyzed using the unpaired *t*-test, and non-normally distributed data using the Mann–Whitney *U* test. Differences in proportions will be assessed with the standard normal deviate (*Z*) test for proportions. Results will be presented as proportions, risk differences, risk ratios, and numbers needed to treat (NNT), each with corresponding 95% confidence intervals (CIs).

*Amended in 25.2.2021, new analysis added: A sensitivity analysis will be performed excluding children with poor cooperation, defined as a mean cooperation score below 4.*

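### Heart-rate and respiratory-rate changes are compared with no covariate, which gives up precision that the recorded pre-treatment value, and to a lesser extent age, would recover

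*Protocol*

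**What the plan says.** Table 3 (Study Objectives) lists among the secondary outcomes "Change in respiratory rate (difference before and after medication" and "Heart rate (difference before and after medication". Both are therefore within-child changes.

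The Statistical analysis section fixes the test: "Continuous variables with normal distribution will be analyzed using the unpaired" *t*-test, "and non-normally distributed data using the Mann–Whitney" *U* test. No covariate is named. The one analysis added later, in 2021, leaves out children who cooperated poorly and adjusts for nothing.

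The information needed for adjustment is collected. Under Treatment of the Enrolled Child in the Emergency Department, the study physician "records the RDAI score as well as other clinical variables listed in Table 3 on the study form", and the assessment is made before treatment as well as after it. Age is known for every child because it is an entry criterion: the trial takes "80 children aged 6 months to 4 years" (Study Population).

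On allocation, the Summary says "Randomization lists for each site will be created using block randomization". No age stratum is mentioned there or under Recruitment and Randomization.

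**The concern.** Heart rate and respiratory rate vary with age, and the age range is eightfold (6 to 48 months). Each child also has a recorded pre-treatment value, which predicts the post-treatment value. A single reading in a distressed child is a noisy measure of that child's usual rate. The raw change subtracts this noise at full weight, whereas a regression on the pre-treatment value gives it the weight that the data support. Because the pre-treatment reading is noisy, age can still carry some information about the post-treatment rate once that reading is in the model.

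At stake is the width of two confidence intervals. Both outcomes bear on the symptom-relief objective. With 40 children per arm and a design sized for RDAI alone, wider intervals than the data allow make a null result on either one harder to interpret.

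**Working it through.** **The plan's own figure.** The Sample Size section concerns RDAI only: difference 2, SD 2.5, power 90%, alpha 5% (taken as two-sided). n = 2 × (1.960 + 1.282)² × 2.5² / 2² = 32.8, so 33 per arm, as stated. 33 / 0.85 = 38.8, so 39 per arm against 40 planned. Both agree with the plan, and nothing below changes them. The protocol gives no SD, correlation or power for heart rate or respiratory rate, so every input from here on is an assumption.

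**General case.** Take equal SDs before and after treatment and pre-post correlation r. The change score has variance 2·SD²·(1 − r); the baseline-adjusted value has SD²·(1 − r²). The share removed by the baseline is (1 − r)/2: 35% at r = 0.3, 25% at 0.5, 15% at 0.7, 10% at 0.8 and 5% at 0.9.

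**Heart rate, with age.** Assumed: age-related SD 10–15 beats/min; other stable between-child SD 8; situational SD 15 before and 12 after treatment; situational correlation 0.2–0.6, giving a covariance c = 36 to 108. Let A be the age variance and S = 64.

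- Change score: 225 + 144 − 2c. It contains no age term.
- Baseline-adjusted: F − C²/B, with B = A + S + 225, F = A + S + 144, C = A + S + c.
- Baseline plus age: the same formula with A removed.

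| Age SD | Correlation | Change | Baseline | Baseline + age | Total cut | Age's cut of remainder |
|---|---|---|---|---|---|---|
| 10 | 0.2 | 297 | 205.2 | 173.4 | 42% | 15% |
| 10 | 0.6 | 153 | 117.8 | 105.6 | 31% | 10% |
| 15 | 0.2 | 297 | 227.5 | 173.4 | 42% | 24% |
| 15 | 0.6 | 153 | 126.4 | 105.6 | 31% | 16% |

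In every row the step from change score to baseline adjustment is more than half of the total. Total interval narrowing is 1 − √0.69 = 17% to 1 − √0.584 = 24%.

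**Sensitivity to the stable SD.** That SD of 8 is as much assumed as the rest. Keeping the age SDs and raising it to 12–15, age removes 4–16% of the remainder. With age SD 5–8 and stable SD 8–15, it removes 1–11%. The total cut also shrinks. At stable SD 15 (S = 225) and c = 108, baseline plus age leaves 369 − 333²/450 = 122.6, which is 20% below 153. At c = 36 it leaves 369 − 261²/450 = 217.6, which is 27% below 297.

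**Respiratory rate, by simulation.** 4,000 runs at 40 per arm. Assumed: ages uniform over 0.5–4 years, level falling 5 breaths/min per year of age, stable SD 6, reading SD 5. Standard errors of the device difference:

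| Effect of treatment | Change | Change + age | Baseline | Baseline + age |
|---|---|---|---|---|
| Fixed fall of 8 | 1.575 | 1.585 | 1.465 | 1.420 |
| 15% fall | 1.599 | 1.600 | 1.381 | 1.349 |
| 30% fall | 1.660 | 1.635 | 1.302 | 1.280 |

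The total variance cut is 1 − (1.420/1.575)² = 19% up to 1 − (1.280/1.660)² = 41%. Age's part of the remainder is 6%, 5% and 3%. Adding age to the raw change gains nothing, or under 2% of the standard error.

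**Age imbalance in the same runs.** The difference in mean age between arms had an SD of about 0.22 years. The change estimate moved by about 0–0.3 breaths/min per year of imbalance with a fixed fall, and by 0.8–1.6 with a proportional fall, against about −4.8 for an unadjusted post-treatment comparison with a fixed fall. The unadjusted change test rejected in 4.5–4.9% of runs under no effect.

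**The case against.** The strongest reply is that nothing here is wrong. An unadjusted comparison of change scores in a 1:1 randomised trial is valid, the outcomes are secondary, and covariates are often left to an SAP, which is not at hand. The validity part stands in full. The deferral part stands only in part: the protocol names the tests for continuous outcomes, so as written the choice is made, though an SAP may refine it.

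A second reply is that age is a small refinement and its size depends on the inputs chosen. That also stands. If only one covariate is added, it should be the pre-treatment value.

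A reader might infer something stronger: that age variation inflates the error term of the planned test, and that a chance age difference between arms distorts the device comparison. The protocol's own outcome definition does not support this. Both outcomes are differences within a child, an additive age effect cancels, and chance imbalance under randomisation is not bias, since the nominal error rate allows for it.

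A reader might also point to the mask: "In children under the age of 3, the spacer is used with a face mask", and Spacer Device Characteristics and Differences gives Babyhaler delivery of 0.8% with a mask and 2.6% without. If 25–40% of children were aged 3 or over (an assumption), the between-arm difference in that share would have an SD of √(2p(1−p)/40), or 9.7–11.0 points, and a gap of 15 points or more would arise in about 12–17% of trials. This does not translate into an error in heart rate or respiratory rate. Older children may go without a mask but need not. The delivery figures suggest a device-by-interface interaction, which an additive age term does not model.

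**Conclusion.** The point holds as a loss of precision in two secondary outcomes. The planned test is valid but less efficient than the collected data allow. Under the assumed heart-rate SDs, a model with the pre-treatment value and age cuts error variance by about 31–42%, so intervals are 17–24% narrower. The cut falls to 20–27% if the stable between-child SD is 15. The assumed respiratory-rate settings give 19–41%. Most of this comes from the pre-treatment value; age adds 1–24% of what remains. If pre and post readings correlate very highly, the gain from the baseline is small (5% at r = 0.9). All these sizes rest on assumed SDs and correlations, because the protocol gives none. The primary outcome, the sample size and the type I error rate are unaffected. This is an optional improvement.

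**What to change.** In Statistical analysis, replace the unpaired test for these two outcomes with one sentence: post-treatment heart rate and respiratory rate will each be analysed by a linear model on device, the recorded pre-treatment value and age at enrolment (continuous, in months), and the adjusted device difference will be reported with its 95% CI. Use the same post-treatment reading that the change score would have used. With the pre-treatment value in the model, taking the change instead of the post-treatment value as the response gives the same device estimate, so the Table 3 definitions can stay.

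The cost is one degree of freedom for each covariate out of about 80 children. No new data, visits or patients are needed. The sentence should be fixed before the group codes are broken.
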